## (6) Rest on Bed (2 minutes)

After the treatment, the patient lies and rests for 2 minutes.

**Table 1. Locations of Acupoints and Meridian for Tuina**

| Acupoints /Meridians   | Location                                                                                                                                                                                                                                                                    |
|------------------------|-----------------------------------------------------------------------------------------------------------------------------------------------------------------------------------------------------------------------------------------------------------------------------|
| Biguan (ST31)   | On the anterior aspect of the thigh, on the line connecting the anterior superior iliac spine and the lower lateral border of the patella, level with the lower border of the symphysis pubis, in the depression on the lateral side of sartorius when the thigh is flexed. |
| Futu (ST32)     | On the anterolateral aspect of the thigh, on the line connecting the lateral end of the base of the patella with the anterior superior iliac spine, 6 cun superior to the base of the patella                                                                               |
| Heding (EX-LE2) | On the anterior aspect of the thigh, in the depression superior to the base of the patella                                                                                                                                                                                  |
| Zusanli (ST36)  | Three cun directly below ST35, and one finger-breadth lateral to the anterior border of the tibia                                                                                                                                                                           |

| Acupoints
/Meridians                | Location                                                                                                                                                                                                                                                                                                                                                                                                                                                                                                                                                                                                                                                                                                                                                                                                                                                                              |
|----------------------------------------|---------------------------------------------------------------------------------------------------------------------------------------------------------------------------------------------------------------------------------------------------------------------------------------------------------------------------------------------------------------------------------------------------------------------------------------------------------------------------------------------------------------------------------------------------------------------------------------------------------------------------------------------------------------------------------------------------------------------------------------------------------------------------------------------------------------------------------------------------------------------------------------|
| Sanyinjiao (SP6)                | On the tibial aspect of the leg, posterior to the medial border of the tibia, 3 cun superior to the prominence of the medial malleolus                                                                                                                                                                                                                                                                                                                                                                                                                                                                                                                                                                                                                                                                                                                                                |
| Xuehai (SP10)                   | On the anteromedial aspect of the thigh, on the bulge of the vastus medialis muscle, 2 cun superior to the medial end of the base of the patella                                                                                                                                                                                                                                                                                                                                                                                                                                                                                                                                                                                                                                                                                                                                      |
| Liangqiu (ST34)                 | On the anterolateral aspect of the thigh, between the vastus lateralis muscle and the lateral border of the rectus femoris tendon, 2 cun superior to the base of the patella                                                                                                                                                                                                                                                                                                                                                                                                                                                                                                                                                                                                                                                                                                          |
| Neixifeng                       | On the anterior aspect of the knee, on the medial patellar ligament                                                                                                                                                                                                                                                                                                                                                                                                                                                                                                                                                                                                                                                                                                                                                                                                                   |
| Waixifeng                       | On the anterior aspect of the knee, on the lateral patellar ligament                                                                                                                                                                                                                                                                                                                                                                                                                                                                                                                                                                                                                                                                                                                                                                                                                  |
| Neixiyan (EX-LE4)               | On the anterior aspect of the knee, in the depression medial to the patellar ligament                                                                                                                                                                                                                                                                                                                                                                                                                                                                                                                                                                                                                                                                                                                                                                                                 |
| Waixiyan (Dubi, ST35)           | On the anterior aspect of the knee, in the depression lateral to the patellar ligament                                                                                                                                                                                                                                                                                                                                                                                                                                                                                                                                                                                                                                                                                                                                                                                                |
| Spleen meridian on the leg      | The leg part of Spleen meridian starts at the lateral side of the big toe, runs along the medial side of the foot crossing the inner ankle. It then travels along the medial side of the lower leg and thighs reaching the pubic bone.                                                                                                                                                                                                                                                                                                                                                                                                                                                                                                                                                                                                                                                |
| Bladder meridian on the leg     | The leg part of bladder meridian runs internally towards the bladder, returns to cross up and down externally on the coccyx region, then continues down the buttock, down the posterior leg towards a point on the medial crease of the posterior knee. The other branch originates from the main branch at the base of the skull and continues downward parallel, but 1 cun more lateral, and continues down until it reaches a point on the middle of the buttock, turns laterally towards a point on the hip, then continues down the posterior leg, crosses through the point on the medial aspect of the posterior knee where the first branch stopped. The two branches join at this point and meridian continues down the back of the lower leg behind the outer ankle, then continues along the outside of the foot and ends on the lateral side of the tip of the little toe |
| Gallbladder meridian on the leg | The leg part of Gallbladder meridian (from lower abdomen and hip) continues to run down the lateral side of the leg, goes over the foot and ends the tip of the fourth toe.                                                                                                                                                                                                                                                                                                                                                                                                                                                                                                                                                                                                                                                                                                           |
| Stomach meridian on the leg     | The leg part of Stomach meridian crosses the abdomen and groin and goes downward along the front of the thigh and the lower leg until it reaches the top of the foot. Finally, it terminates at the lateral side of the tip of the second toe.                                                                                                                                                                                                                                                                                                                                                                                                                                                                                                                                                                                                                                        |

[figure not shown]

**Figure 2. Locations of Acupoints for Tuina**

**Note:** Biguan (ST31), Futu (ST32), Liangqiu (ST34), Waixiyan (Dubi, ST35), Zusanli (ST36); Heding (EX-LE2), Neixiyan (EX-LE4), Xuehai (SP10), Sanyinjiao (SP6). The picture copyright authorization has been obtained from 3Dbody

[figure not shown]

**Figure 3. Meridian selected in Tuina**

**Note:** A: Bladder meridian on the leg; B: Gallbladder meridian on the leg; C: Spleen meridian on the leg; D: Stomach meridian on the leg. The picture copyright authorization has been obtained from 3Dbody

## **2. Comparative group: manual Physical Therapy**

After enrollment, practitioner will evaluate the initial musculoskeletal status, range of motion. The mPT group mainly includes 5 steps: stretching, soft tissue manual therapy, physiological movements, accessory movements and strength training.

### **(1) Stretching Manual (3 minutes)**

The practitioner stretches the quadriceps, iliopsoas, hamstrings, adductor femoris, abductor femoris (iliotibial band, tensor fascia lata and gluteus muscles) and gastrocnemius.

### **(2) Soft Tissue Manual (10 minutes)**

The practitioner alternates the manual therapy of kneading (using fingers or the palm of the hand to knead the muscles and soft tissues around the knee joint) and pressure (using fingers or the palm of the hand to apply pressure on tender points or tense soft tissues around the knee joint). The above manual therapies are performed on the areas of the quadriceps, hamstrings, adductor femoris, abductor femoris and gastrocnemius, suprapatellar and peripatellar, medial and lateral capsule, with the requirement that the movements be gentle and slow to avoid causing pain or injury to the patient. The process is repeated 1min/time, with each area being operated 2 minutes.

### **(3) Grade 3 or 4 Physiological Movements (3 minutes)**

**Knee Flexion** The practitioner stabilizes the patient's thighs and knees and grabs the patient's ankle. The patient's heel is softly moved towards the hip of the restricted movement disorder. And oscillation can be performed in the bending direction. The practitioner could increase both valgus or varus stress and internal or external rotation as needed.

**Knee Extension** The practitioner places one hand on the patient's patella and the other on the back of their ankle. Keeping their arms straight, the practitioner tilts their body towards the patient's head and lifts the patient's feet off the bed, allowing for mobilization of the knee joint with internal or external rotation or the ankle joint with varus or valgus stress.

#### **Accessory movements (2 minutes)**

**The definition of Grade 3 or Grade 4 by Maitland motabilitation: Grade 3: Large slow amplitude oscillatory movements performed from the middle to the end of the available joint range. Grade 4: Small slow amplitude movements up to the end of the available joint play.**

**Femoro-Tibia Articulation Mobilizations (0.5 minutes)** Long axis traction: The patient sits in front of the practitioner while the practitioner stands opposite the affected limb. Both knees are flexed to 90°, and the practitioner places one hand on the back of the thigh to match the bent knee while holding the patient's heel with the other hand. The patient's calf is then placed between the practitioner's biceps and shoulder and fixed firmly, while both hands of practitioner are kept fixed at the knee bend. The practitioner tracts the legs downwards towards the floor.

**Anterior to Posterior / Posterior to Anterior-Accessory Movements (0.5 Minutes)** The patient lies in supine position with their knee flexed and extended as tolerated. The practitioner places their 1st web space on the patient's proximal tibia and applies oscillatory mobilization (Grade 3 or 4) in an anterior-posterior (AP) direction on the proximal tibia-. The manipulation was performed with large slow amplitude oscillatory movements from the middle to the end of the available joint range with Grade 3. If needed, the practitioner can add tibial rotation to effectively reach the restrictive barrier with Grade 4. The practitioner grasps around the proximal tibia and produces an AP movement with their thenar eminence of the lateral hand, while simultaneously producing a posterior-anterior movement with their fingers of the medial hand. This technique results in a lateral rotation of the tibia on the femur.

**Medial to Lateral/ Lateral to Medial Accessory Movements (0.5 minutes)** The practitioner stabilizes their lateral hand over the distal lateral femur, placing it between their medial forearm and trunk. They place their medial hand on the proximal tibia and apply a lateral push while the lateral hand applies a medial push to the proximal tibia. Then oscillatory mobilization (Grade 3 or 4) is applied in a medial to lateral or lateral to medial direction on the proximal tibia. The manipulation was performed with large slow amplitude oscillatory movements from the middle to the end of the available joint range with Grade 3. If needed, the practitioner can add the small slow amplitude movements up to the end of the available joint play with Grade 4.

**Patellar Mobilizations (0.5 minutes)** The practitioner stands with their back facing the patient and places the affected leg between their upper arm and trunk, holding the distal leg with both hands. Then they slightly pull the leg down while simultaneously swinging the leg up.

**(4) Strength Training (2 minutes)**

**Straight Leg Raise** The patient lies in supine position, lifts the leg about 0.5 meters off the bed, followed by tightening the quadriceps muscles and keeping the knee locked. After holding the leg for 15-30 seconds, and then lower the leg. The process is repeated 2~3 times, for 1 minute in total.

**Cycling in the Air** The patient lies in supine position with both knees up to form 90°, and keep both hands on the head. Crunch up and twist across the body while simultaneously performing a bicycle motion with the legs. The process is repeated for 1 minute.

**(5) Rest on Bed (2 minutes)**

**4. Attention: Treatment During the Trial**

Patients could take medications for KOA if necessary or if taking it for a long time. The treatments such as massage, acupuncture, and other physical therapies, are prohibited during the treatment period. The medications or other treatments for KOA during the trial must be recorded in the CRF.

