## **Study Design**

### **1. Overview of Study Design**

This trial is a single-center parallel active-controlled, blinded randomized controlled trial that aims to compare the effectiveness of Tuina and mPT. A total of 140 qualified KOA patients will be randomly divided into either the Tuina group or mPT group at a ratio of 1: 1. In the Tuina group, patients will receive the Tuina therapy, and patients in the mPT group will receive joint mobilization, soft tissue manipulations, passive stretching, and strength training. They will both receive a total of 8 treatments in a 3-week course. Additionally, both groups will be provided health education and home-exercise instruction. Evaluations will be conducted at baseline (week 0) and 4 and 16 weeks. The primary outcome is the related symptoms of KOA, and secondary outcomes include health-related quality of life, treatment satisfaction, physical limitation, emotional and psychological stress, and adverse events. Figure 1 describes the flow chart of these procedures.

The study consists of 5 phases: recruitment, selection, baseline, treatment, and follow-up.

[figure not shown]

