**Figure 1 The flow chart**

**Recruitment:** Recruitment will be through multimodal strategies, (posters at the outpatient and community service centers, e-poster online, etc.);

**Selection (week -1):** Any patients who will be screened will be completing the case screening form. Those who met the screening criteria will be subsequently referred to a specialist for diagnosis and differential diagnosis. Ultimately, the eligible cases were enrolled in the study.

**Baseline (week 0):** Patients who satisfied the inclusion and exclusion criteria will be identified, randomly allocated, and completed the baseline evaluation period.

**Treatment (week 0-4):** Patients will be scheduled to be treated by practitioners for 8 sessions over 3 weeks, according to the randomization assignment;

**Follow-up (week 5-16):** Follow-up assessment will be operated by evaluators.

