#### 4. The Target Number of Participants and Estimation Basis

- (1) Estimation of the number of patients: The following is assumed using the reference literature of prior studies to estimate the number of patients.
- (2) Level of significance,  $\alpha_{\text{two-sides}} = 0.05$ .
- (3) Type 2 error ( $\beta$ ) is set to 0.2, and the power of the test is set to 80%.
- (4) Based on our pilot study and the previous studies about the minimal clinically important difference (MCID) [28, 29], we assumed that the primary outcome (a total WOMAC score at 4 weeks) in Tuina group was expected to have mean difference of 7 to mPT with a standard deviation for both groups of 13.
- (5) Compliance: 80% (the ratio expected to receive treatment 8 times or more during the 3-week treatment period).
- (6) Sample size calculation for the trial by using PASS 15 (Power Analysis and Sample Size Software (2017). NCSS, LLC. Kaysville, Utah, USA, [ncss.com/software/pass](http://ncss.com/software/pass).)

As a result of applying (1), (2), (3), (4), and effect size, the sample size is calculated to be 140 in total, 70 patients in each group.

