### **Study Interventions**

The practitioners must have a medical certificate and has treated patients with KOA for more than 5 years. Furthermore, they will receive the training of standardized operation procedures before treatment. Both groups receive 20-minutes treatment with 8 sessions over a 3-week treatment period.

**Routine Treatment** It conducted in both Tuina and mPT groups. Routine treatment includes health education, self-management and home-exercise instruction, and they will be encouraged to perform the simple home-based exercise.

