### **7. Outcome Definitions**

**Primary Outcome** The change in the total Western Ontario and McMaster University Osteoarthritis Index (WOMAC) from baseline to 4 weeks

**Secondary Outcomes** The secondary outcomes covered pain, physical function, and patients' overall assessment of disease severity.

- **Pain Dimensions** WOMAC pain (the change between the baseline and 4, 8, and 16 weeks), the worst knee pain in the last 24 hour using NRS(the change between the baseline and 4, 8, and 16 weeks) ;

- **Function Dimensions** the average function of previous week using WOMAC function (the change between the baseline and 4, 8, and 16 weeks), WOMAC stiffness (the change between the baseline and 4, 8, and 16 weeks), 30 Second Time Chair Rise Test (the change between the baseline and week 4), Timed Up and Go Test Time (the change between the baseline and week 4), One Leg Standing Test (the change between the baseline and week 4);
- **Patients' overall assessment of disease severity:** the 12-item Short Form Health Survey (the change between the baseline and 4, 8, and 16 weeks), the patient global assessment (the change between 4, 8, and 16 weeks);
- **Criteria of Response Rate:** The OMERACT-OARSI responder criteria to assess the response rate of treatment for KOA at 4 weeks.
- **The blinding assessment**

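### The bar on outside massage, acupuncture and physical therapy is tied to the treatment period; if that is 3 weeks, it lapses one week before the week-4 primary WOMAC

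*Supplement*

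**What the plan says.** The rule on concomitant treatment is in the protocol, Study Interventions, item 4 (Attention: Treatment During the Trial): "The treatments such as massage, acupuncture, and other physical therapies, are prohibited during the treatment period". The same item lets patients take medication for knee osteoarthritis (KOA) and adds: "The medications or other treatments for KOA during the trial must be recorded in the CRF".

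The protocol describes the length of treatment in several places:

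- Overview of Study Design: "They will both receive a total of 8 treatments in a 3-week course".
- Sample-size section, compliance item: "the ratio expected to receive treatment 8 times or more during the 3-week treatment period".
- Opening of Study Interventions: "Both groups receive 20-minutes treatment with 8 sessions over a 3-week treatment period".
- Outcome Measures, introduction: the first evaluation, at 4 weeks, is deliberately set one week after treatment so that local soreness from the treatment does not affect it.
- Flow-chart text (Figure 1): the phase labels open "Treatment (week 0-4" and "Follow-up (week 5-16", although the treatment entry itself still schedules the 8 sessions over 3 weeks.

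The primary outcome is the change in WOMAC total from baseline to week 4. Table 4 of the amended protocol allows each visit one week either side. SAP section 7 describes one component of the total as "the average function of previous week using WOMAC function". The May 2019 amendments do not alter the rule on outside treatments, and no other section extends it.

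**The concern.** Outside massage and physical therapy are the same kind of hands-on care that the trial compares. If they are allowed in the week before the primary assessment, WOMAC at week 4 can move for reasons other than the assigned treatment. Because the rule applies equally to both arms, the expected effect is extra variability or a weaker contrast between arms.

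Two other parts of the protocol suggest that the gap was not intended. Exclusion criterion 9 bars patients who had acupuncture, massage or manipulation in the 3 months before entry, so these therapies are regarded as able to affect the outcome. The one-week delay before assessment exists to let treatment soreness settle, and outside manual therapy in that week works against this purpose.

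**Working it through.** This is a calendar check with one supporting ratio.

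**Inputs**

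- End of the bar: week 3 (sample-size section, Study Interventions) or week 4 (flow-chart label).
- Primary visit: nominally week 4, allowed from 4 − 1 = 3 to 4 + 1 = 5 (Table 4).
- Recall for WOMAC function: 1 week (SAP section 7).
- Mean baseline WOMAC in the 127 patients with the primary outcome: total 19.26, function 13.13 (Additional file 5).

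**The plan's own timeline.** Three weeks of treatment plus the stated one-week delay gives 3 + 1 = week 4, which is the primary time point. The Outcome Measures section therefore agrees with treatment ending at week 3.

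**Unprotected time** = visit week − week in which the bar ends, with a floor of 0.

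**Share of the function recall unprotected** = min(1 week, unprotected time) / 1 week.

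| Visit at | Gap, bar ends week 3 | Recall share | Gap, bar ends week 4 | Recall share |
|---|---|---|---|---|
| Week 3 | 3 − 3 = 0 | 0% | 0 | 0% |
| Week 4 | 4 − 3 = 1 week | 100% | 4 − 4 = 0 | 0% |
| Week 5 | 5 − 3 = 2 weeks | 100% | 5 − 4 = 1 week | 100% |

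On the 3-week reading, the week that the function score describes at a nominal visit is exactly the week in which outside therapy is allowed.

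**Weight of the function score in the primary outcome.** 13.13 / 19.26 = 68.2% of the mean baseline total. This comes from observed trial data. It shows that the affected component is the larger part of the total, and it says nothing about how often outside therapy was used.

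**Do other provisions close the gap?**

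- Recording in the case report form (CRF) makes use visible but does not prevent it. The primary model in SAP section 8 adjusts for medication and has no term for non-drug treatment.
- The sensitivity analysis in SAP section 9 keeps patients who completed treatment without major protocol violations. Therapy taken after the bar has ended breaks no rule, so this analysis would not remove it.

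**The case against.** The strongest reply is that the flow-chart text is the only place that gives the treatment phase calendar limits, and those limits are weeks 0 to 4. If the rule refers to that phase, the nominal primary visit is covered and the problem is an undefined term. This is a fair reading, and it is why the finding is conditional. It does not settle the matter. The opening of Study Interventions, under the same heading as the rule, uses the words treatment period for 3 weeks, as does the sample-size section. Even on the flow-chart reading, a visit at week 5 has one unprotected week.

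Other points stand in part:

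- **No demonstrated effect.** The documents give no rate of outside therapy and no estimate of what it does to WOMAC. The percentages above describe opportunity, not use. This is correct and limits the finding to a minor one.
- **The sensitivity analysis.** SAP section 9 does not define a major violation, so outside therapy might not be removed even when it is barred. That is also correct. Closing the gap makes such use a deviation but does not guarantee exclusion.
- **Existing safeguards.** Randomisation, blinding of patients, evaluators and statisticians, and CRF recording all help. They protect against differential use or make use visible, but they do not stop it or bring it into the analysis.
- **Week 3 is nominal.** Treatment may be suspended until symptoms resolve, so some patients will finish later and have a shorter gap.
- **Pragmatic choice.** Allowing and recording ordinary care after delivery is defensible for the later follow-up visits. It is harder to defend for the single week before the primary assessment, which the protocol deliberately keeps free of trial treatment.

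**Conclusion.** The point holds, as a minor one. On the better-supported 3-week reading, the bar ends 1 week before the nominal primary visit (0 to 2 weeks across the window), and at a nominal visit that is the whole week described by WOMAC function. On the weeks 0 to 4 reading the gap is 0 at a nominal visit and up to 1 week at a late one.

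The conclusion assumes that sessions finish on schedule. It uses the recall period that the SAP states for function; the documents give none for pain or stiffness. No bias between arms is claimed. Any noise or dilution is likely to be small and cannot be sized from the documents. The sample size and the choice of primary analysis are not affected.

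**What to change.** Reword the rule in Study Interventions, item 4, along these lines:

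> Massage, acupuncture and other physical therapies for the knee are prohibited until the week-4 assessment is completed.

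Tying the bar to the actual assessment removes the ambiguity over the treatment period and covers late visits. Optionally, tabulate outside therapy recorded in the CRF by arm and visit as description only, with no change to the analysis.

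The cost is one sentence. On the 3-week reading patients are restricted for about one more week, or two for a late visit. On the weeks 0 to 4 reading there is no added restriction at a nominal visit and up to one week at a late one. The optional table uses data that the protocol already requires.
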